**2.5 Final visit**

Assessments will be undertaken according to schedules in 2.6.

*2.5.1 Reimbursement*

Regular payments will be made to all participants to cover their travel expenses and any inconvenience caused. At the end of the study all participants will have received remuneration of 5.000 SEK if they participated in the whole study. If they did not participate in the whole study they will receive the respective proportion of remuneration. Those who have to attend for additional visits will be reimbursed accordingly. During the study participants will receive latex condoms free of charge. If any medication is required as a result of the study, this will also be provided free of charge.

*2.5.2 In the event of discontinuation*

A subject may withdraw his/her consent to participate in the study at any time without prejudice or for other reasons, see section 3.7. Whenever possible, the tests and evaluations listed for the termination visit should be carried out if the subject refuses follow-up according to the protocol visit schedule. The DSMC should be notified of all study withdrawals within 48 hours. Subjects who withdraw from the study will be replaced only as long as the study is still open for enrolment. No replacement will be allowed when the enrolment is closed. All subjects who receive at least one immunization will be included in the safety analysis. If a subject does not complete the immunization schedule following a serious adverse event or toxicity, he or she will continue to be followed according to the protocol visit schedule, and, as a minimum, until the adverse event/toxicity is resolved and/or the cause is identified. A genuine effort will be made to determine the reason(s) why a subject fails to return for the necessary visits. If the subject is unreachable by telephone, at least one registered letter will be sent to the subject requesting contact with the clinic. This information will be recorded on the appropriate source document.

**2.6 Procedural Flow Chart**

| Study Visit | 1 | 2 | 3 | 4 | 5 | 6 | 7 | 8 | 9 | 10 | 11 | 12 | 13 | 14 | 15 | 16 | 17 |
| --- | --- | --- | --- | --- | --- | --- | --- | --- | --- | --- | --- | --- | --- | --- | --- | --- | --- |
| Week | a | b | 0 | 2 | 6 | 8 | 12 | 14 | 16 | 32 | 36 | 38 | 40 | 60 | 62 | 64 | 72 |
| Recruitment, medical record number, Screen form 1  Study Consent  Risk Assessment  Study Consent 2  Abbreviated risk assessment | X  X  X | X  X |  |  |  |  |  |  |  |  |  |  |  |  |  |  |  |
| Immunizations |  |  | X |  | X |  | X |  |  |  | X |  |  | X |  |  |  |
| Complete History / Physical examination *Including weight(kg), height (cm),*  *arm circumf.(cm)*  Interim H&P (AE elicitation)  Risk behaviour counselling  Randomisation  ECG  *Genital swabs or urine for Neisseria gonorrhoeae, and chlamydia trachomatis will be collected if indicated according to clinical signs and symptoms* | X  X | X | X  X | X | XX | X | XX | X | XX | X  X |  |  | X  X |  | X  X |  | X  X |
| Punch biopsy* |  |  |  |  |  |  |  | X | X |  |  |  |  |  |  |  |  |
| HIV antibody/antigen test  Syphilis, HBV & HCV  CD4 counts  HIV RNA / DNA PCR*  WBC with differential  Chem. Pathology  Troponin I  Urine analysis; urine dipstick for protein/blood  Urine test of female volunteers for pregnancy (UPT)  Urine, saliva, semen, vaginal and rectal wash* | X  X  X  X  X  X  X  X | X  X  X  X | X  X | X  X  X | X  X  X  X | X  X  X | X  X  X  X | X  X  X  X | X  X  X  X  X  X | X  X  X | X  X | X | X  X  X | X  X | X  X  X  X  X |  | X  X  X  X  X  X |
| Binding and neutralizing antibodies, incl. Anti-vaccinia Ab (red top)  IFN-gamma ELISPOT, fresh cells (Na-heparin, green top)  8-colour ICS, fresh cells (Na-heparin, green top)  Lymphoproliferation assay, fresh cells (Na-heparin, green top)  Multi-colour ICS, cryo-preserved cells (Na-heparin, green top)  Cryo-preserved cells* (Na-heparin, green top)  HLA analysis* (EDTA, purple top)  *Volume for immunogenicity*  **)optionally* |  | X  X  X  X  X  X  *100* | X  (X)  (X)  (X)  X  X  X  *100* |  |  | X  X  (X)  X  X  X  *100* | X | X  X  (X)  X  X  X  *100* | X | X | X  X  X  X  X  X  *100* | X  X  (X)  X  X  X  *100* | X  X  X  (X)  X  X  *100* | X  X  X  X  X  X  *100* | X  X  (X)  X  X  X  *100* | X  X  X  (X)  X  X  *100* | X  (X)  (X)  (X)  X  X  *80* |
| TOTAL BLOOD VOLUME (ml) | 60 | 110 | 110 | 10 | 10 | 110 | 20 | 110 | 35 | 20 | 100 | 100 | 110 | 100 | 110 | 100 | 110 |

## 3 Procedures

**3.1 Blood and urine collection**

Blood will be collected using a sterile needle, usually from the ante-cubital fossa, according to the schedule and transported to the appropriate laboratories. Urine will be collected into a sterile container as indicated on the schedule and either transported to the appropriate laboratory or tested by a member of the clinical team according to trial specific standardised operating procedures. The optional collection of saliva (spitting or collection in a swab), vaginal secretions (by an absorbent device) or rectal washings (instillation of 200 ml NaCl) will be performed according to a standardized protocol and frozen.

The total estimated volume of donated blood is estimated to 1325 ml during the study; approximately 76 weeks.

- All biological samples to be analysed by the clinical laboratory will be collected and processed according to institutional guidelines and regulations regarding biobanks.

- All samples sent to the laboratories at the Swedish Institute for Infectious Disease Control will be labelled with the following information

Medical record number: Subject initials:

Study day: Visit number:

Date

Type of sample (serum, plasma, blood etc)

All samples for routine haematology and biochemistry will be labelled according to hospital rules with the full study subject identity.

Samples that will be analysed after freezing should be prepared, labelled, and stored at the appropriate temperature. Specimens that are shipped will be correctly prepared, labelled, and kept at the correct temperature.

**3.2 Clinical history and examination**

A past medical history will be collected at the screening visit, including details of any previous reaction to vaccination, history of epileptic fit, exposure to vaccinia, and contraceptive and smoking practices. The general examination will include weight (kg), height (cm), blood pressure, and inspection of the skin to exclude severe eczema and checked for the presence of an electroporation scar, a vaccinia scar, respiratory, cardio-vascular and abdominal systems examination. An assessment of cervical and axillary lymph nodes will also be undertaken. The examination results and history of exposure to vaccinia will be recorded on the case record form.

**3.3 Genital infection screen**

The following will be collected in all participants

- serology for syphilis
- markers of hepatitis B and hepatitis C infection

The following will be collected if indicated on account of risk and symptoms, according to trial specific clinical standardised operating procedures:

- urethral, vaginal, cervical and rectal specimens as appropriate for Neisseria gonorrhoeae
- collection of urine for Chlamydia trachomatis

**3.4 Pre-HIV test screen and counselling**

Study personnel will assess volunteers for past and current risk of HIV infection using the screening proforma and counsel them prior to collecting blood for an HIV test. The counselling process will ensure that volunteers have sufficient knowledge about HIV infection to understand what the test is for, the implications of a positive, negative and equivocal result and the standard of care available for HIV infection locally. They will also be informed how and when they will receive the result, according to the local policy in each clinical centre.

**3.5 Safer sex counselling and condom provision**

Participants will be counselled by study personnel about the importance of condoms at screening and reminded on the day of each immunisation. Hypo-allergenic condoms will be provided free of charge to participants throughout the trial.

**3.6 HIV related issues**

Please see section 6 for details of the procedures that may be required in the event of:

- A request for an HIV test
- HIV infection
- Social discrimination as a result of post-vaccine response
- The possibility of a false positive test result in a standard HIV test

**3.7 Discontinuation procedures (including withdrawal and stopping the study)**

Participants may withdraw at any time if they wish to do so, for any reason. The date of withdrawal and reason for doing so should be recorded in the appropriate case record form.

The clinical investigator may decide that it is not in the best interests of the participant to proceed to the next immunisation following an adverse event (see below). The discontinuation and reason should be recorded in the appropriate immunisation and reportable adverse event case record forms, which should be forwarded to DSMC and sponsor within the next 2 working days. Trial visits should carry on at least until resolution or stabilisation of the event, but ideally up to the last visit in the schedule, provided the participant is willing. The frequency of visits and laboratory investigations may be reduced or increased on consultation with the Principal Investigator or Trial Management Group (see section 7).

*3.7.1 Criteria for withdrawal of subjects from injection schedule*

Under certain circumstances, a subject will be terminated from participating in further injections. These events include:

1. HIV infection.
2. Grade 2 events classified as probably associated with immunization that in the view of the clinician or the volunteer are unacceptable.
3. Grade 3 or 4 adverse events classified as probably associated with immunizations.
4. Type 1 hypersensitivity associated with immunization.
5. Serious intercurrent illness that is not expected to resolve prior to next scheduled immunization.
6. Any condition that could put the volunteer at risk or hamper the evaluation of subsequent immunizations.
7. Need for systemic glucocorticoids or other immunomodulators than NSAIDs for any reason.
8. Repeated failure to comply with protocol requirement.
9. The Sponsors, vaccine provider or principal investigator decide to stop or cancel the study.
10. The ethics committee or Medical Products Agency request that the study be stopped.

Patients who are discontinued from additional study injections will continue to be followed according to the schedule to further evaluate safety and monitor adverse events.

*3.7.2 Criteria for stopping the study*

The Principal investigator will closely monitor and analyse study data as they become available and will make determinations regarding the presence and severity of the adverse events. The administration of study injections and new enrolments will be halted if one subject develops a grade 3 event assessed as, possibly, or probably related to the vaccination or experiences a grade 4 or 5 (death) SAE assessed as possibly, related to the vaccination. Safety data and changes in study status should be submitted to the ethics committee in case the study is stopped. In the case that the trial is stopped or halted, this will be reported to the MPA by using the form obtained from the EudraCT system.

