**3.8 Unblinding procedure**

The PI or his deputy may ask the monitor to unblind an individual who develops a grade 3, 4 or 5 (death) SAE assessed as possibly related to the vaccination if it is in the volunteers best interest. The monitor may be asked to compile interim data for example for the regulatory authorities in Tanzania. Such data should remain blinded to the study staff and participants, but should be supplied to the DSMC. The DSMC will not be demanded to act on such data unless there are safety issues. When all volunteers have finished the DNA immunizations the monitor and statistician will compile group safety and immunological data while study staff and volunteers remain blinded.

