**5.2 Relationship to study product**

This can be classified as:

**None** adverse events felt to be due to extraneous causes that neither follow a known pattern of response nor a reasonable temporal relationship to study product

**Remotely related** adverse events that are unlikely to be related to product but which follow a reasonable temporal relationship, such that this cannot be completely excluded or events that could be associated with product but which are unrelated in time

**Possibly related** adverse events that may be due to extraneous causes but which follow a known pattern of response and/or a reasonable temporal relationship to study product

**Probably related** adverse events that cannot be explained by extraneous causes; which follow a know pattern of response and/or a reasonable temporal relationship; which disappear or decrease on cessation of study product and reappear on re-challenge

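### Section 5.2 makes re-challenge an unconditional part of 'probably related': on one reading withdrawal criteria 2 and 3 miss a first event, on the other the grade 4/5 halt does not name its class (minor)

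*Protocol*

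**What the plan says.** Section 3.7.1 lists ten circumstances that end a participant's further injections. Two depend on attribution and grade:

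- criterion 2: "Grade 2 events classified as probably associated with immunization that in the view of the clinician or the volunteer are unacceptable";
- criterion 3: "Grade 3 or 4 adverse events classified as probably associated with immunizations".

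Section 5.2 is the only causality scale in the protocol. Its classes are none, remotely, possibly and probably related. *Possibly* needs a known response pattern and/or plausible timing. *Probably* needs three things, separated by semicolons: no extraneous explanation; a known pattern and/or plausible timing; and events "which disappear or decrease on cessation of study product and reappear on re-challenge".

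Section 3.7.2 is the trial-wide stop. Injections and enrolment are "halted if one subject develops a grade 3 event assessed as, possibly, or probably related to the vaccination", or if a subject "experiences a grade 4 or 5 (death) SAE assessed as possibly, related to the vaccination". Section 3.8 lets the PI request unblinding for a "grade 3, 4 or 5 (death) SAE assessed as possibly related to the vaccination".

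**The concern.** The withdrawal criteria and the halting rule depend on the class names in 5.2, and the highest class has an element that a first event cannot show. Re-challenge in this trial means the next scheduled immunisation. Taken at face value, the two criteria written for graded, vaccine-related events would become available only after the volunteer had been exposed again.

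Separately, the two limbs of one sentence in 3.7.2 name different classes: the grade 3 limb names two, the more serious limb only the weaker one. Safety and tolerability are the primary objective, so two clinicians with the same event in front of them should reach the same answer from these rules.

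**Working it through.** No calculation applies; this is a check of one set of wording against another.

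**Step 1: what 5.2 requires.** The second element of *probably* uses and/or, so alternatives are marked where they are meant. The third joins resolution on stopping to recurrence on re-challenge with a plain *and*, and does not say that this applies only if re-challenge occurs. The cumulative reading is the natural one. A reading as typical features is possible.

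**Step 2: what re-challenge means here.** Doses are given at weeks 0, 6, 12, 36 and 60 (section 1.2). A reaction first seen after the week 0 dose could be re-challenged at week 6 at the earliest.

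**Step 3: follow a first event through each reading.**

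| First event | Elements cumulative | Elements illustrative |
|---|---|---|
| Highest class it can reach | possibly | probably |
| Criterion 2 (unacceptable grade 2) | cannot apply | applies if rated probably |
| Criterion 3 (grade 3 or 4) | cannot apply | applies if rated probably |
| Halt, grade 3 limb | applies (possibly) | applies (either class) |
| Halt, grade 4/5 limb (SAE) | applies (possibly) | applies if possibly; not literally named if probably |

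Each column has a gap, and the gaps fall in different rows. On the cumulative reading a first grade 4/5 SAE judged *possibly* related is exactly what 3.7.2 names. A death cannot be re-challenged, so it could never leave that class for *probably*.

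**Step 4: is the missing class in 3.7.2 deliberate?** Six rules use *possibly* or *possible* as a causality class:

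| Rule | Also names probably? |
|---|---|
| 3.7.2, grade 3 limb | yes |
| 3.7.2, grade 4/5 limb | no |
| 3.8, unblinding | no |
| 5.3, grade 2 | yes |
| 5.3, grade 3/4 | yes |
| 7.7.1, additional DSMC review | yes |

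Four of six name it and two do not. The grade 4/5 limb also has a stray comma after *possibly*. A dropped word is the likely explanation.

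**Step 5: what else can stop dosing.**

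- The list in 3.7.1 is introduced as inclusive, so it is open.
- Criterion 4 covers type 1 hypersensitivity.
- Criterion 6 covers "Any condition that could put the volunteer at risk or hamper the evaluation of subsequent immunizations".
- Section 3.7 lets volunteers withdraw whenever they wish, and lets the clinical investigator decide that "it is not in the best interests of the participant to proceed to the next immunisation following an adverse event".
- Section 5.3 sends every grade 3/4 event that is at least remotely related to the PI, who decides on discontinuation.
- Section 3.7.2 halts the trial after one *possibly* related event (grade 3, or a grade 4/5 SAE).
- Section 7.6.1 lets the Steering Committee end the trial, and 7.7.1 calls a DSMC meeting for any reportable SAE.

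None of these needs the *probably* class.

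**The case against.** The strongest reply is that the protocol itself points to the illustrative reading. If *probably* required an earlier reaction and a repeat dose, naming it in the grade 3 limb of 3.7.2 would be almost redundant, because the first grade 3 event would already have halted the trial as *possibly* related. Section 5.3 also treats *probably* as an ordinary rating for a newly reported event. This is a fair inference about intent. It does not clear the text, because on that reading the gap moves to the grade 4/5 limb.

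The second reply is that criterion 2 is itself a matter of judgement. It turns on whether the clinician or volunteer finds the event unacceptable, and both can already stop dosing under 3.7 whatever the causality class. That stands, and leaves little practical gap for grade 2 events.

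The third is that staff would take *possibly* in 3.7.2 as a minimum. That is likely, and is why this is a wording fault with a small consequence.

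A reader might go further and infer that a volunteer must be dosed again before being withdrawn, or that a fatal related event would leave the trial running. The documents support neither. Several provisions stop an individual's injections without the *probably* class, and SAEs go to the monitor and DSMC the same working day under 5.3. Nor can both harms be claimed for one first event, since each needs the reading that removes the other.

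**Conclusion.** The point holds as a minor drafting fault. Whichever way 5.2 is read, one stated safety trigger fails on its wording for events it is evidently meant to catch: criteria 2 and 3 of 3.7.1 (2 of 10) on the cumulative reading, or the grade 4/5 limb of 3.7.2 on the illustrative one. The omission in 3.8 is of the same kind but matters less, because that section only permits unblinding.

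This assumes that *associated* in 3.7.1 means *related* in 5.2, which is reasonable because no other scale is given, and that re-challenge means a further study dose. The effect on participants is limited by the provisions in step 5 of the working: what is weak is the wording of the specific triggers, and safeguards are not absent.

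**What to change.** Make these changes in one amendment:

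- **Section 5.2:** replace the last clause of *probably related* with wording such as *and, if re-challenged, reappear*, so that a first event can be placed in that class.
- **Section 3.7.2:** in the grade 4/5 limb, write *possibly or probably related*.
- **Section 3.8:** for consistency, use the same wording for SAEs of grades 3 to 5.

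The first two belong together. Correcting 5.2 alone would settle the text on the reading under which first grade 4/5 SAEs can fall in a class that the halt does not name.

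These edits do not change how *possibly* related events are handled. A grade 3 event that stays in that class remains outside criterion 3, and whether that volunteer continues if dosing resumes is still the PI's decision under 5.3.

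The cost is a few words of text, with no added visits, procedures or data.

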**4 Assessments**

**4.1 Safety assessments**

The subject will be contacted the day after each immunization by the investigator, study nurse, or research assistant to obtain local and systemic reaction data and to determine the subject's clinical status.

Subjects will be instructed to call the specified study personnel immediately if any unusual or severe sign or symptom appears after immunization. These subjects should be seen in the clinic at the time of maximal symptoms, if possible, and will be followed up clinically until resolution of symptoms.

An adverse event is any undesired, noxious or pathological change in a patient or subject as indicated by physical signs, symptoms, and/or laboratory changes that occurs following administration of one of the vaccines, whether or not considered vaccine related. This definition includes intercurrent illnesses or injuries, and exacerbation of pre-existing conditions. The Steering Committee will arrange for a compilation of safety data when 10 subjects have received the electroporation. These data will be reviewed by the monitor for accuracy and submitted to the DSMC and Sponsor.

*4.1.1 Local adverse events*

Following the intradermal injections the site will be graded as dry, moist or wet. The presence or absence of a weal will be recorded. The pain will be recorded as none (0), mild (1), moderate (2), severe (3) or extreme (4). Following the electroporation the pain will be recorded as none (0), mild (1), moderate (2), severe (3) or extreme (4). Following the MVA pain in the muscle injected will be graded by the participant as none (0), mild (1), moderate (2), severe (3) or extreme (4).

This will be recorded in the appropriate case record form or once the participant has left the clinic, in the diary card.

Redness will be recorded as the maximum diameter in cm and graded on this criteria and the presence of symptoms according to the appended scale. Participants will be asked to record any discomfort and any medication taken for relief of symptoms.

Clinical staff will complete the case record form following eachimmunisation. Completed caserecord forms and the diary cards will be sent to the study nurse at Venhälsan to be recorded in the database. In the event that there are two observations on the same day, those confirmed at a visit will take precedence over diary card observations in the analysis.

Study personnel should verify all grade 3 or 4 events and record the findings in the source documents.

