**5.1 Definitions**

An adverse event is any adverse experience occurring during the course of the study including the screening period.

Criteria for grading clinical and laboratory events are listed in the appendix.

The severity of events reported on the adverse event form will be determined by the investigator, based on the Toxicity Grading Scale or if the event is not listed the event will be graded following these guidelines:

Mild (Grade 1): Transient or mild discomfort. No limitation in normal daily activity.

Moderate (Grade 2): Some limitation in normal daily activity.

Severe (Grade 3): Unable to perform normal daily activity.

Serious (Grade 4): Life threatening

Death (Grade 5)

A severe adverse event is one graded 3 or 4 by criteria in appendix. Some, but not all grade 3 and 4 adverse events will be “serious” by ICH GCP criteria below.

*5.1.1 Serious Adverse Events (SAEs)*

An adverse event is considered to be a “serious adverse event” by ICH Good Clinical Practice (ICH GCP) criteria if it results in the following:

- death,
- a threat to life,
- requires in-patient hospitalisation or prolongs existing hospitalisation (hospitalisation for elective treatment of a pre-existing condition is not included),
- results in persistent or significant disability or incapacity,
- is a congenital anomaly (i.e., the outcome of pregnancy involving a participant), or
- is any other important medical condition*.

*Examples of conditions regarded as “any other important medical condition” include allergic bronchospasm requiring intensive emergency treatment, seizures or blood dyscrasias which did not result in hospitalisation or development of drug dependency.

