**5.3 Reporting adverse events**

Adverse events should be recorded on the appropriate case record form as to the nature of the event, the time it started and ended, the severity, probable relationship to the drug and any medication taken.

Grade 2 events probably or possible related to the vaccine should be discussed in the weekly Trial Management Group meetings.

Any grade 3 or 4 adverse event remotely, possibly or probably related to the immunization should immediately be reported to the PI or his deputy, who will fill in the appropriate forms and decide discontinuation of the vaccination schedule. The PI should if indicated arrange for urgent review of the case by the Steering Committee and report this to the monitor and the DSMC within 2 working days. The monitor will confirm that the event is potentially reportable and inform the Sponsor. Should the case be considered reportable by the DSMC, a report will be prepared by the clinical investigator or his deputy and filed with the Sponsor, Medical Products Agency and the Regional Ethics Committee.

**SAEs** should be reported to the monitor and the DSMC the same working day that the Clinical Investigator becomes aware of the event. This can be done by telephone or fax. The minimum criteria required in reporting a SAE are the participant identifiers (trial number/ date of birth/initials), reporting source (name of Investigator), and why the adverse event is identifiable as serious.

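### The automatic study halt in section 3.7.2 covers a related non-serious grade 3 event but, as worded, not a related non-serious grade 4 event

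*Protocol*

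**What the plan says.** The only rule that halts the whole study automatically is in Protocol section 3.7.2; section 7.7.3 merely refers back to it. The trigger is one participant with a "grade 3 event assessed as, possibly, or probably related to the vaccination or experiences a grade 4 or 5 (death) SAE". The relatedness wording of the second limb ends "SAE assessed as possibly, related to the vaccination", so it names only possible relatedness, whereas the grade 3 limb names possible and probable.

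Section 5.1 separates severity from seriousness: "Some, but not all grade 3 and 4 adverse events will be" serious by the ICH GCP criteria. It also gives a general definition, "Serious (Grade 4): Life threatening", for events that are not on the Toxicity Grading Scale. Section 4.1.1 sets out pain scales that run to 4, for example "Following the electroporation the pain will be recorded as none (0), mild (1), moderate (2), severe (3) or extreme (4"), with matching scales for the intradermal injection and the MVA boost.

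The neighbouring rules treat grades 3 and 4 alike without asking for seriousness:

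- Section 3.7.1, item 3, withdraws a participant for "Grade 3 or 4 adverse events classified as probably associated with immunizations".
- Section 5.3 says "Any grade 3 or 4 adverse event remotely, possibly or probably related to the immunization should immediately be reported to the PI", who will then "decide discontinuation of the vaccination schedule".
- Section 7.7.1 calls an extra DSMC meeting for a related grade 3 or 4 event that is still unresolved after 72 hours.

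Section 3.8 (unblinding) does require an SAE, but equally for grades 3, 4 and 5.

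**The concern.** A single-event halting rule should never become harder to trigger as severity rises. Here the seriousness condition appears only from grade 4 upward, so a worse event can escape a halt that a milder one would cause.

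The primary question of the trial is whether DNA immunisation with electroporation is safe and tolerable, and pain after the procedure is one of the main things being measured. For a non-serious event on a listed scale, the halt is mandatory at grade 3. At grade 4 it is left to the judgement of the investigator, the Steering Committee or the DSMC.

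**Working it through.** **Step 1. Apply section 3.7.2 to each case.** Cross seriousness (yes/no) with relatedness (possibly/probably), which gives 2 × 2 = 4 related combinations per grade. Read the word for possible relatedness in the second limb as a minimum.

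| Grade | Serious? | Limb met | Automatic halt |
|---|---|---|---|
| 3 | No | First | Yes (2 combinations) |
| 3 | Yes | First | Yes (2 combinations) |
| 4 | Yes | Second | Yes (2 combinations) |
| 4 | No | None | No (2 combinations) |

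Grade 3 is covered in 4 of 4 combinations and grade 4 in 2 of 4. Grade 5 is death, hence always an SAE, and is covered. Read strictly, the second limb also omits probably related SAEs, which would leave 1 of 4 covered at grade 4. That omission is most likely a slip.

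**Step 2. Can a grade 4 event be non-serious under this protocol?** For an unlisted event, no: grade 4 means life threatening, and a threat to life is an SAE criterion in section 5.1.1. For a listed event, yes: section 5.1 says so in general terms. The pain scales in section 4.1.1 are a visible case, because extreme pain need not meet any of the seriousness criteria.

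**Step 3. Does another rule supply the halt?**

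- Section 3.7.1, item 3: one participant only, and only for probable relatedness.
- Section 5.3: a report to the principal investigator and a decision, not a halt.
- Section 7.7.1: a DSMC meeting, not a halt. A non-serious event must persist beyond 72 hours, which short-lived procedure pain would not.
- Section 3.7.1, item 9, and section 7.6.1: the sponsor, vaccine provider, investigator or Steering Committee may stop the trial, at their discretion.

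None is an automatic study-wide halt.

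**Step 4. How often is a visible 0 to 4 pain scale used?** Group sizes and schedule come from the design table in section 1.2: four groups of 12, three priming visits and two boosts, with B3 boosted intradermally with electroporation. Counting one rating per visit and procedure:

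- Intradermal injection: 48 × 3 + 12 × 2 = 168
- Electroporation (B2, B3 and B4 at priming, B3 at boost): 36 × 3 + 12 × 2 = 132
- Intramuscular boost: 36 × 2 = 72, assuming that saline boosts are rated like MVA because of blinding
- Total: 168 + 132 + 72 = 372

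Check: 168 + 72 = 240 = 48 × 5 immunisation visits. These are opportunities for a score, not a measure of risk.

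**Step 5. Illustrative chance that the gap is met.** The protocol gives no grade 4 rate. Assume that each of the 48 participants independently has probability p of a related, non-serious event first recorded at grade 4, and that all are immunised without an earlier halt. The chance of at least one is 1 − (1 − p)^48.

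| p | Chance of at least one |
|---|---|
| 0.1% | 4.7% |
| 0.5% | 21% |
| 1% | 38% |
| 2% | 62% |

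**The case against.** The strongest reply is that nobody would read the rule this way. A protocol that halts for one possibly related grade 3 event plainly means to halt for anything worse, and the SAE wording resembles that of section 3.8, so it may be stock text. That is probably right about intent. It does not change what the sentence says, and a mandatory halt with a report to the Medical Products Agency should not depend on staff reading past its words.

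Second, the uncovered case depends partly on a grading appendix that is not shown. Unlisted grade 4 events are serious by definition. The investigator determines severity and staff verify grade 3 and 4 events, so a raw pain score of 4 may not translate directly into a grade 4 adverse event. This stands as a limit on how wide the gap is. It does not close it, because section 5.1 itself allows non-serious grade 4 events.

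Third, an event recorded at grade 3 before worsening would already have caused the halt. That is true, but it does not help where a single score is taken after the procedure.

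Fourth, the probabilities use assumed rates and ignore earlier halts for grade 3 events. This is fair. If, as a further assumption, grade 3 first has probability 3% per participant and grade 4 first 1%, the chance that a grade 4 event precedes any halt is about (1/4) × (1 − 0.96^48) = 21%, against 38% without that competition. Neither figure is evidence of a rate.

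Finally, the discretionary safeguards are real and would probably act on an alarming event. They still leave to judgement at grade 4 what is automatic at grade 3.

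**Conclusion.** The concern holds. As written, section 3.7.2 is not monotone in severity: it covers 4 of 4 related combinations at grade 3 and 2 of 4 at grade 4, and both uncovered ones are non-serious. This follows from sections 3.7.2 and 5.1 alone, with the pain scales of section 4.1.1 as the visible example.

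The practical gap is narrow. It concerns events graded on a listed scale, first recorded at grade 4, and not meeting any seriousness criterion. How often that would occur cannot be derived from the protocol; the range of 4.7% to 62% rests wholly on the assumed p of 0.1% to 2% and on no earlier halt. No endpoint or group comparison is affected. Because the fault lies in an operative safety rule, it should be corrected rather than left to interpretation.

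**What to change.** Replace the trigger in section 3.7.2 with a single limb, for example: *Injections and enrolment are halted when any participant has an adverse event of grade 3 or higher, serious or not, judged possibly or probably related to vaccination.* This removes the reversal and restores the missing reference to probable relatedness in the same edit. Section 7.7.3 follows automatically because it points to 3.7.2, and section 3.8 needs no change.

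The cost is one sentence, with no new data or staff. The only downside is a possible extra halt, with its report to the Medical Products Agency, for something like brief extreme pain. A related grade 3 event already has that consequence.
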